| 12-lead ECG                             | 1        |                    |                   |                    |                                                |
| Serum Biomarkers                        | 16       | 16                 |                   |                    |                                                |

- 1 – All baseline measurements must be done within 14 calendar days prior to start of treatment administration unless otherwise specified.
- 2 – See section 5.1 for guidelines for elevated serum troponin.
- 3 – Archived Tissue to be obtained and sent unstained paraffin-embedded tissue (from the most recent tumor block available).  
Investigators should make efforts to collect and ship one block or 15-20 slides. See Section 9.5 for details.
- 4 – within -3 days
- 5 – Height should be obtained at baseline
- 6 – Vital signs include temperature, blood pressure, respiratory rate, and heart rate (weight only needs to be obtained every odd cycle)
- 7 – Repeat only if > 3 calendar days since last eval/test
- 8 – If ANC < 1500 or plts < 100,000, CBCs/differentials will be repeated twice a week until counts are recovered (ANC ≥1500 or plts ≥100,000) per protocol. If counts are recovered (ANC ≥1500 or plts ≥100,000) on day of scheduled drawing do not repeat till next protocol schedule day.
- 9 – CBC with differential count and platelet count
- 10 – Na, K, HCO3, Ca, glucose, BUN, creatinine, total bilirubin, SGOT, SGPT, alkaline phosphatase, albumin, GGT, total protein
- 11 – within -5 calendar days (MRI should be obtained and evaluated prior to start of new cycle)
- 12 – Collect for at least 30 days post last dose of AT-101. Patients who are discontinued due to an AE will be followed until AE resolves.
- 13 – repeat only if > 14 days since date of last scan
- 14 – Needs to be drawn after the last dose of AT-101 in each treatment cycle
- 15 – Needs to be drawn the last day of treatment
- 16 – Serum Biomarkers are being collected within 24 hours before the first dose of AT-101 and after one week of therapy (any time during week 2 of cycle 1). See Section 9.5.2 for details.

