## **9.2 Adverse Event Definition and Reporting**

Patients will be evaluated for toxicity if they have received at least one dose of AT-101.

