### **9.2.2 Recording of Adverse Events - ABTC AE Form**

- **Document on ABTC Adverse Event Form**
  - **Using AdEERS Application**
- 1) **CTCAE term (AE description) and grade:** The descriptions and grading scales found in the revised NCI Common Terminology Criteria for Adverse Events (CTCAE) version 4.0 will be utilized for AE reporting beginning January 1, 2011. All appropriate treatment areas should have access to a copy of the CTCAE version 4.0. A copy of the CTCAE version 4.0 can be downloaded from the CTEP web site (<http://ctep.cancer.gov>).
  - 2) The Investigator will monitor each patient closely for the development of adverse events and toxicities and record all such events on the ABTC AE Form. Each single sign or symptom must be reported separately. The DCTD/NCI Common Terminology Criteria for Adverse Events, CTCAE v.4.0 will be employed to record these toxicities beginning January 1, 2011. **A copy of the CTCAE version 4.0 can be downloaded from the CTEP home page (<http://ctep.cancer.gov>). All appropriate treatment areas should have access to a copy of the CTCAE version 4.0. You must use one of the CTCAE criteria to define your event.**
  - 3) Adverse events not included in the CTCAE v.4.0 should be reported and graded under the Other adverse event within the appropriate category and grade 1 to 5 according to the general grade definitions, mild, moderate, severe, life-threatening, fatal or disabling, as provided in the CTCAE or the CTCAE Manual. For new adverse events, the investigator may use the Adverse Event Module, Appendix I of the CTCAE, v.4.0. Also, new adverse events may be submitted to the CTEP Help Desk for annual evaluation by the CTCAE Change Management Committee.
  - 4) Abnormal lab results which are graded by NCI CTCAE v.4.0 will be recorded on ABTC Laboratory Checklist, along with documented attribution, not on AE form. However, if an action was conducted due to this abnormality (e.g. RBC transfusion due to low Hgb) this would be recorded on the AE form also.

All adverse events should be followed up in accordance with good medical practice. Abnormalities of laboratory events which, in the opinion of the Investigator, constitute adverse events (even if not serious) should be followed.

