**9.3 Comprehensive Adverse Events and Potential Risks Lists (CAEPRs)**

**Comprehensive Adverse Events and Potential Risks list (CAEPR)  
for  
(R)-(-)-Gossypol acetic acid (AT-101) (NSC 726190)**

The Comprehensive Adverse Event and Potential Risks list (CAEPR) provides a single list of reported and/or potential adverse events (AE) associated with an agent using a uniform presentation of events by body system. In addition to the comprehensive list, a subset, the Agent Specific Adverse Event List (ASAEL), appears in a separate column and is identified with ***bold*** and ***italicized*** text. This subset of AEs (ASAEL) contains events that are considered 'expected' for expedited reporting purposes only. Refer to the 'CTEP, NCI Guidelines: Adverse Event Reporting Requirements' [http://ctep.info.nih.gov/protocolDevelopment/default.htm#adverse\\_events\\_adeers](http://ctep.info.nih.gov/protocolDevelopment/default.htm#adverse_events_adeers) for further clarification. *Frequency is provided based on 230 patients.* Below is the CAEPR for (R)-(-)-Gossypol acetic acid (AT-101).

Version 2.1, January 6, 2010

| Adverse Events with Possible
Relationship to (R)-(-)-Gossypol acetic acid (AT-101)
(CTCAE 4.0 Term)
[n= 230] |                                                                  |                        | EXPECTED AEs FOR
ADEERS REPORTING

Agent Specific Adverse
Event List
(ASAEL) |
|-----------------------------------------------------------------------------------------------------------------------|------------------------------------------------------------------|------------------------|---------------------------------------------------------------------------------------------|
| Likely (>20%)                                                                                                         | Less Likely (<=20%)                                              | Rare but Serious (<3%) | Expected                                                                             |
| BLOOD AND LYMPHATIC SYSTEM DISORDERS                                                                           |                                                                  |                        |                                                                                             |

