# A Phase 2 Study of R-(-)-gossypol (Ascenta's AT-101) in Recurrent Glioblastoma Multiforme

NABTT #: 0702

NCI #: NABTT 0702

Principal Investigator: [name]

|                                                        |                              |  |                               |
|--------------------------------------------------------|------------------------------|--|-------------------------------|
|                                                        | Blood bilirubin increased    |  |                               |
|                                                        | Cardiac troponin I increased |  |                               |
|                                                        | Cardiac troponin T increased |  |                               |
|                                                        | Creatinine increased         |  |                               |
|                                                        | Weight loss                  |  | Weight loss            |
|                                                        | White blood cell decreased   |  |                               |
| METABOLISM AND NUTRITION DISORDERS              |                              |  |                               |
| Anorexia                                               |                              |  | Anorexia               |
|                                                        | Dehydration                  |  | Dehydration            |
|                                                        | Hypocalcemia                 |  |                               |
|                                                        | Hypokalemia                  |  | Hypokalemia            |
|                                                        | Hypomagnesemia               |  | Hypomagnesemia         |
| MUSCULOSKELETAL AND CONNECTIVE TISSUE DISORDERS |                              |  |                               |
|                                                        | Back pain                    |  |                               |
|                                                        | Pain in extremity            |  |                               |
| NERVOUS SYSTEM DISORDERS                        |                              |  |                               |

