### **11.3 Secondary Objectives**

1. To assess the acute and late toxicities associated with the treatment. The proportion of patients with serious or life threatening toxicities will be estimated along with 95% confidence intervals. The frequency of different type toxicities will be tabulated by each cycle of the treatment.
2. To estimate tumor response rate. The probability of tumor response (definition: section 8.1) will be estimated using binomial distribution along with 95% CI.
3. To estimate a 6-month progression-free survival rate. The 6-month progression-free survival is defined as patient who is alive and disease progression free at the time of 26-week (6 months) from first day of the treatment (definition of disease progression: section 10.0). The probability of 6-month progression-free survival will be estimated using binomial distribution.
4. Correlative study: Apoptosis can be triggered through either the intrinsic (mitochondrial) or extrinsic (receptor) pathways. The study will focus on regulators of both the intrinsic (Bcl-2, Bcl-XL, Mcl-1, Bax, Bak) and extrinsic (FLIP, survivin, XIAP) pathways. Serum will be collected for analysis of apoptotic protein levels immediately before the first dose and after one week of therapy. Every effort will be made to collect tumor tissue before and after treatment. Descriptive statistics will be used to summarize the protein expressions and patient's MGMT methylation status.

The Cox's proportional hazard model will be used to explore the association between change of the proteins and patient's survival status.

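### Magnesium is missing from the scheduled chemistry panel although hypomagnesemia is listed as possibly related to AT-101, so its tabulated frequency will be under-ascertained by an unknown amount

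*Protocol*

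**What the plan says.** The table in Protocol section 9.1 schedules serum chemistry at baseline, before every odd and even cycle, and at the off-treatment visit. Footnote 10 fixes its content: "Na, K, HCO 3 , Ca, glucose, BUN, creatinine, total bilirubin, SGOT, SGPT, alkaline phosphatase, albumin, GGT, total protein". This is a closed list of 14 analytes. LDH and troponin have rows of their own, and nothing else in the protocol schedules a magnesium test.

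The adverse event table in section 9.3, based on 230 patients, contains "Hypomagnesemia" among the events possibly related to AT-101, in the column for events at 20% or less. The term is repeated in the expected-event (ASAEL) column. That subset "contains events that are considered 'expected' for expedited reporting purposes only".

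Three further statements govern how such an event reaches the analysis:

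- Section 9.2.2, on recording: "Abnormal lab results which are graded by NCI CTCAE v.4.0 will be recorded on ABTC Laboratory Checklist".
- Section 9.2, on who is counted: "Patients will be evaluated for toxicity if they have received at least one dose of AT-101".
- Section 11.3, item 1, on the analysis: "The frequency of different type toxicities will be tabulated by each cycle of the treatment".

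**The concern.** A laboratory toxicity enters this dataset only through a laboratory result. Potassium and calcium are measured in every patient at every scheduled draw, so a low value is found whether or not the patient has symptoms. Magnesium is measured only if a site decides to order it. A dosed patient who is never tested still counts in the denominator and looks the same as a patient with normal magnesium. The tabulated frequency of hypomagnesemia therefore mixes the drug's effect with local ordering habits, and it errs downward.

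Estimating toxicity is the first secondary objective, and a later analysis plan cannot recover values that were never measured. A second, smaller consequence is that an unmeasured case of grade 3 or higher would also be missing from the toxicity rate in the section 11.4 interim rule.

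**Working it through.** The protocol states no figure on this point, so there is none to reproduce. The check is a comparison of two lists, followed by an illustration of size.

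**Step 1: blood-chemistry events in the possible-relationship table of 9.3 against the tests in 9.1.**

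| Event in 9.3 | Scheduled test in 9.1 |
|---|---|
| ALT and AST increased | SGPT and SGOT, footnote 10 |
| Alkaline phosphatase increased | footnote 10 |
| Bilirubin increased | footnote 10 |
| Creatinine increased | footnote 10 |
| Troponin I and T increased | own row |
| Hypocalcemia | Ca, footnote 10 |
| Hypokalemia | K, footnote 10 |
| Hypomagnesemia | none |

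Hypocalcemia is not in the expected-event column and is measured. Hypomagnesemia is in that column and is not measured.

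**Step 2: direction of the error.** Let p be the true proportion of patients with hypomagnesemia of any grade, and m the share of those patients whose magnesium is measured off schedule. With all dosed patients in the denominator:

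tabulated rate = p × m

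This is below p whenever p > 0 and m < 1. With magnesium in the scheduled panel, m is close to 1 and the tabulated rate is close to p.

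**Step 3: illustration.** N = 56 is the planned sample size (section 3.1), taking every patient as dosed. The values of p and m are assumptions; the protocol gives neither. Expected patients counted, N × p × m, with the tabulated rate in brackets:

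| Assumed p | All cases (56 × p) | m = 0 | m = 25% | m = 50% |
|---|---|---|---|---|
| 5% | 2.8 | 0 | 0.7 (1.25%) | 1.4 (2.5%) |
| 10% | 5.6 | 0 | 1.4 (2.5%) | 2.8 (5%) |
| 20% | 11.2 | 0 | 2.8 (5%) | 5.6 (10%) |

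Rounded, the true totals are about 3, 6 and 11 patients. The 20% row is the ceiling of the column in 9.3, not an estimate for this event.

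**Step 4: the interim rule.** Section 11.4 suspends the study if the lower 95% confidence bound on the rate of grade 3 or higher toxicity exceeds 18% in the first 25 patients. The method for the bound is not named. Assume exact binomial limits and a count of patients:

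- Two-sided: 9/25 gives a lower limit of 17.97% and 10/25 gives 21.1%, so the rule is first met at 10.
- One-sided: 8/25 gives 17.0% and 9/25 gives 20.2%, so the rule is first met at 9.

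One unmeasured case changes the outcome only if the count stands one short of the boundary and that patient has no other grade 3 or higher toxicity. The protocol gives no grade 3 or higher rate for hypomagnesemia, so the chance of this cannot be calculated.

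**The case against.** The strongest reply is that nothing here is a contradiction. No section promises a scheduled test for every listed event. The list in 9.3 collects reported and potential events, and its expected column settles expedited-reporting status, not laboratory content. That is right. A reader might infer that being listed as expected creates a duty to monitor, and the protocol does not say so. The point rests instead on the possible-relationship entry combined with the planned tabulation.

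Other stronger readings also fail:

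- **That hypomagnesemia cannot be found, or would go unnoticed.** Adverse event evaluation is scheduled before every cycle and off treatment. Section 9.2.1 counts abnormal laboratory findings as adverse events, and the recording rule in 9.2.2 is not confined to the footnote 10 analytes. Section 5.1 also expects electrolyte abnormalities to be found and corrected. A magnesium result ordered locally would be recorded. The event is under-ascertained, not invisible.
- **That magnesium is the only gap in the whole of 9.3.** Hyperuricemia is also listed there and uric acid is not scheduled. It appears only among events whose relationship to AT-101 is undetermined. Uniqueness holds for the possible-relationship table alone.
- **That comparison with the 230-patient list is spoiled.** Section 11.3 plans no such comparison, and the protocol does not say how magnesium was measured in those patients.
- **That 3, 6 or 11 patients would be missed.** Those are assumed totals of any grade. The number missed depends on off-schedule testing, which is unknown.

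The objection that only one row of a descriptive secondary table is at stake is nearly correct. The one addition is the remote effect on the interim toxicity rule.

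**Conclusion.** The point holds as a minor one. Followed as written, the protocol measures every blood-chemistry event in its possible-relationship table except hypomagnesemia, then tabulates toxicities by type and cycle. The frequency for hypomagnesemia will be too low if any cases occur and some of those patients are not tested off schedule. The amount cannot be stated from the protocol; the illustration only shows that it could range from nothing to several patients out of 56.

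The conclusion assumes that the tabulation uses all dosed patients, as section 9.2 implies, and that no magnesium test is scheduled outside the protocol. The primary survival endpoint, the 52 events, the power and the section 11.5 decision rule are untouched.

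**What to change.** Reconcile footnote 10 with the table in 9.3 by adding magnesium to the chemistry panel at the draws already scheduled, including baseline so that low values present before treatment can be recognised. The cost is one extra analyte per draw, with no new visit or procedure.

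If the panel is left as it is, report hypomagnesemia with the number of patients tested as the denominator and state beside it that magnesium was not measured systematically. This fallback is weaker. If sites test mainly patients with symptoms, a rate among those tested may overstate the frequency, so the number tested and the number dosed should both be shown.

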## **9.2 Adverse Event Definition and Reporting**

Patients will be evaluated for toxicity if they have received at least one dose of AT-101.

### **9.2.1 Definition - Adverse Event**

Adverse event is defined as any unfavorable and unintended sign (including an abnormal laboratory finding), symptom or disease temporally associated with the use of a medical treatment or procedure regardless of whether it is considered related to the medical treatment or procedure (attribution of unrelated, unlikely, possible, probable, or definite).

### **9.2.2 Recording of Adverse Events - ABTC AE Form**

- **Document on ABTC Adverse Event Form**
  - **Using AdEERS Application**
- 1) **CTCAE term (AE description) and grade:** The descriptions and grading scales found in the revised NCI Common Terminology Criteria for Adverse Events (CTCAE) version 4.0 will be utilized for AE reporting beginning January 1, 2011. All appropriate treatment areas should have access to a copy of the CTCAE version 4.0. A copy of the CTCAE version 4.0 can be downloaded from the CTEP web site (<http://ctep.cancer.gov>).
  - 2) The Investigator will monitor each patient closely for the development of adverse events and toxicities and record all such events on the ABTC AE Form. Each single sign or symptom must be reported separately. The DCTD/NCI Common Terminology Criteria for Adverse Events, CTCAE v.4.0 will be employed to record these toxicities beginning January 1, 2011. **A copy of the CTCAE version 4.0 can be downloaded from the CTEP home page (<http://ctep.cancer.gov>). All appropriate treatment areas should have access to a copy of the CTCAE version 4.0. You must use one of the CTCAE criteria to define your event.**
  - 3) Adverse events not included in the CTCAE v.4.0 should be reported and graded under the Other adverse event within the appropriate category and grade 1 to 5 according to the general grade definitions, mild, moderate, severe, life-threatening, fatal or disabling, as provided in the CTCAE or the CTCAE Manual. For new adverse events, the investigator may use the Adverse Event Module, Appendix I of the CTCAE, v.4.0. Also, new adverse events may be submitted to the CTEP Help Desk for annual evaluation by the CTCAE Change Management Committee.
  - 4) Abnormal lab results which are graded by NCI CTCAE v.4.0 will be recorded on ABTC Laboratory Checklist, along with documented attribution, not on AE form. However, if an action was conducted due to this abnormality (e.g. RBC transfusion due to low Hgb) this would be recorded on the AE form also.

All adverse events should be followed up in accordance with good medical practice. Abnormalities of laboratory events which, in the opinion of the Investigator, constitute adverse events (even if not serious) should be followed.

### 9.2.3 Relationship

The Investigator must document his/her opinion of the relationship of the event to study medication as follows:

- *Unrelated*  
The adverse event is clearly not related to the investigational agent(s).
- *Unlikely*  
The adverse event is doubtfully related to the investigational agent(s).
- *Possible*  
The adverse event may be related to the investigational agent(s).
- *Probable*  
The adverse event is most likely related to the investigational agent(s).
- *Definite*  
The adverse event is clearly related to the investigational agent(s).

**9.3 Comprehensive Adverse Events and Potential Risks Lists (CAEPRs)**

**Comprehensive Adverse Events and Potential Risks list (CAEPR)  
for  
(R)-(-)-Gossypol acetic acid (AT-101) (NSC 726190)**

The Comprehensive Adverse Event and Potential Risks list (CAEPR) provides a single list of reported and/or potential adverse events (AE) associated with an agent using a uniform presentation of events by body system. In addition to the comprehensive list, a subset, the Agent Specific Adverse Event List (ASAEL), appears in a separate column and is identified with ***bold*** and ***italicized*** text. This subset of AEs (ASAEL) contains events that are considered 'expected' for expedited reporting purposes only. Refer to the 'CTEP, NCI Guidelines: Adverse Event Reporting Requirements' [http://ctep.info.nih.gov/protocolDevelopment/default.htm#adverse\\_events\\_adeers](http://ctep.info.nih.gov/protocolDevelopment/default.htm#adverse_events_adeers) for further clarification. *Frequency is provided based on 230 patients.* Below is the CAEPR for (R)-(-)-Gossypol acetic acid (AT-101).

Version 2.1, January 6, 2010

| Adverse Events with Possible
Relationship to (R)-(-)-Gossypol acetic acid (AT-101)
(CTCAE 4.0 Term)
[n= 230] |                                                                  |                        | EXPECTED AEs FOR
ADEERS REPORTING

Agent Specific Adverse
Event List
(ASAEL) |
|-----------------------------------------------------------------------------------------------------------------------|------------------------------------------------------------------|------------------------|---------------------------------------------------------------------------------------------|
| Likely (>20%)                                                                                                         | Less Likely (<=20%)                                              | Rare but Serious (<3%) | Expected                                                                             |
| BLOOD AND LYMPHATIC SYSTEM DISORDERS                                                                           |                                                                  |                        |                                                                                             |
|                                                                                                                       | Anemia                                                           |                        |                                                                                             |
| GASTROINTESTINAL DISORDERS                                                                                     |                                                                  |                        |                                                                                             |
|                                                                                                                       | Abdominal distension                                             |                        | Abdominal distension                                                          |
| Abdominal pain                                                                                                        |                                                                  |                        | Abdominal pain                                                                |
|                                                                                                                       | Constipation                                                     |                        | Constipation                                                                  |
| Diarrhea                                                                                                              |                                                                  |                        | Diarrhea                                                                      |
|                                                                                                                       | Dry mouth                                                        |                        | Dry mouth                                                                     |
|                                                                                                                       | Dyspepsia                                                        |                        |                                                                                             |
|                                                                                                                       | Gastritis                                                        |                        |                                                                                             |
|                                                                                                                       | Gastrointestinal disorders - Other
(pneumatosis intestinalis) |                        | Gastrointestinal disorders -
Other (pneumatosis intestinalis)             |
|                                                                                                                       | Ileus                                                            |                        | Ileus                                                                         |
| Nausea                                                                                                                |                                                                  |                        | Nausea                                                                        |
|                                                                                                                       | Small intestinal obstruction                                     |                        | Small intestinal obstruction                                                  |
| Vomiting                                                                                                              |                                                                  |                        | Vomiting                                                                      |
| GENERAL DISORDERS AND ADMINISTRATION SITE CONDITIONS                                                           |                                                                  |                        |                                                                                             |
|                                                                                                                       | Edema limbs                                                      |                        |                                                                                             |
| Fatigue                                                                                                               |                                                                  |                        | Fatigue                                                                       |
|                                                                                                                       | Fever                                                            |                        |                                                                                             |
| INFECTIONS AND INFESTATIONS                                                                                    |                                                                  |                        |                                                                                             |
|                                                                                                                       | Infections and infestations – Other
(Infection – Select)      |                        | Infections and infestations –
Other (Infection – Select)                  |
| INVESTIGATIONS                                                                                                 |                                                                  |                        |                                                                                             |
|                                                                                                                       | Alanine aminotransferase
increased                            |                        | Alanine aminotransferase
increased                                        |
|                                                                                                                       | Alkaline phosphatase increased                                   |                        |                                                                                             |
|                                                                                                                       | Aspartate aminotransferase
increased                          |                        | Aspartate aminotransferase
increased                                      |

